### Study endpoints

#### Primary endpoint

Composite of non fatal stroke (including strokes with new tissue-based definition), non fatal major coronary event and cardiovascular death.

Secondary endpoints:

Rate of patients who meet the recommended guideline targets regarding blood pressure, smoking cessation, serum-LDL, physical activity, HbA1c (in patients with diabetes), therapeutic range of INR or regular intake of new oral anticoagulants in patients with atrial fibrillation,

Effects on vascular surrogate parameters (microalbuminuria, physical fitness,)

Total mortality

Frequency of hospital admissions for vascular diseases (including TIA, angina pectoris with vascular interventions, peripheral arterial occlusive disease with vascular intervention)

Number of days “alive and at home”.

#### *Substudy endpoints*

Effects on vascular surrogate parameters (intima-media-thickness status of retinal fundus “cerebrovascular lesion load” in MRI), effects on quality of life and mood, cost effectiveness, correlation between risk factor control, surrogate parameters and biomarkers (exploratory).

### Power and sample size calculation

The expected event rate in the control arm was estimated on the basis of the results of more recently published studies [2,3,6,17]. The expected relative risk reduction was calculated in a conservative way only on the basis of blood pressure reductions and irrespective of additional effects of other risk factor modifications.

The effect size (relative risk reduction) was estimated on the basis of the observed effects of blood pressure reduction in recent secondary prevention trials [1,18] and the mean blood pressure differences between two consecutive cohorts evaluated in the Charité hospitals in Berlin [19]. The first cohort was observational and represented standard care in Berlin. The second cohort underwent a stepwise modeled support program that included up to four outpatient appointments over a period of 6 months, using the same strategies as described above. The basis of the sample size estimation is an expected event rate of 16.94% after three years in the control group and a relative risk reduction of 28% in the intervention group resulting from relative risk reductions per mmHg in other secondary prevention studies. The sample size was calculated assuming an aimed power of 80%. After consideration of a non-adherence rate of 10% in the intervention group and a drop-out rate of 5% in both arms, the case number results in 2.082 patients (1.041 patients per group).

After analysis of mean blood pressure differences in the 1-year follow-up of the first 500 patients, the expected effect size and the power calculation will be re-adjusted.

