**Methods/design:**

Patients with acute TIA or minor stroke admitted to the participating stroke centers are screened and recruited during in-hospital stay. Patients are randomised in a 1:1 ratio to intervention (support program) and control (usual care) arms. Inclusion of 2.082 patients is planned. The support program includes cardiovascular risk factor measurement and feedback, monitoring of medication adherence, coaching in lifestyle modifications, and active involvement of relatives. Standardized motivational interviewing is used to assess and enhance patients’ motivation. Primary objective is a reduction of new major vascular events defined as nonfatal stroke and myocardial infarction or vascular death. Recruitment time is planned for 3.5 years, follow up time is at least 2 years for every patient resulting in a total study time of 5 years (first patient in to last patient out).

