### Statistical analysis

The primary analysis is a time to event analysis using Cox-regression-models. An interim analysis after 160 observed events will be done by a statistician blinded to the study arm. The interim analysis will indicate whether the sample size and study duration has to be modified according to the overall observed event rate. The sample size needs not to be adjusted for this blinded interim analysis as only the overall event rate will be considered. The assessment of the true drop out rate will be part of the (blinded) interim analysis. The dichotomized secondary endpoints will be evaluated according to the primary outcome measure. Continuous variables will be analyzed with the appropriate tests. The clustering of the data by the different centres will be accounted for by using frailty models [20].

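### On the stated three-year basis, at an assumed two-sided 5% and with non-adherence diluting the effect, 2,082 patients give about 76–77% power; the 80% should be restated for the planned Cox analysis

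*Protocol article*

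**What the plan says.** Under Power and sample size calculation, the protocol article takes an "expected event rate of 16.94% after three years in the control group and a relative risk reduction of 28% in the intervention group". The aimed power is 80%. The total of 2,082 (1,041 per group) is reached "After consideration of a non-adherence rate of 10% in the intervention group and a drop-out rate of 5% in both arms". The section does not give alpha, sidedness, a hazard ratio or a number of events, nor how the 10% entered the calculation.

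Under Statistical analysis: "The primary analysis is a time to event analysis using Cox-regression-models". Under Recruitment and randomization, recruitment lasts 3.5 years, every patient is followed for at least 2 years, and the total duration is given as 5 years.

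**The concern.** Drop-out and non-adherence act differently on power. A patient who drops out removes information, so the sample is divided by the retained fraction. A non-adherent patient stays in the randomised comparison and pulls the arms together, so the required size grows with the inverse square of the diluted difference. Adding a flat percentage for non-adherence is too little.

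The stated 1,041 per group is exactly what a flat 20% addition to the undiluted size produces. If that is how it was obtained, 80% overstates the power on the article's own three-year basis. The trial's feasibility, and later the reading of a null result, would then be judged against too favourable a figure. The planning basis is also a three-year proportion, while the power of the Cox analysis depends on the number of events over the whole follow-up.

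**Working it through.** **Inputs from the article:** control risk p1 = 0.1694 at three years; relative risk reduction 28%; power 80%; non-adherence 10% (intervention arm); drop-out 5% (both arms); 1,041 per arm, 1:1; recruitment 3.5 years; total 5 years, or 5.5 if every patient has 2 years.

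**Assumed:** two-sided 5%; no benefit in non-adherers; drop-outs contribute nothing; constant hazard and uniform accrual for the Cox calculations.

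**1. Reproducing the stated size.** Intervention risk p2 = 0.72 × 0.1694 = 0.12197; mean risk p̄ = 0.14568.

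n = [1.960 √(2p̄(1−p̄)) + 0.842 √(p1(1−p1) + p2(1−p2))]² / (p1 − p2)²
= [1.960 × 0.49892 + 0.842 × 0.49779]² / 0.04743² = 867.2 per arm.

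867.2 × 1.20 = 1,040.7, rounded up to 1,041. The 20% would be 10% + 5% + 5%. Other head-count inflations miss: 867.2/(0.90 × 0.95) = 1,014; 867.2/0.85 = 1,020; 867.2/0.80 = 1,084.

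**2. Non-adherence as dilution, three-year basis.** p2 = 0.9 × 0.12197 + 0.1 × 0.1694 = 0.12671, a risk reduction of 25.2%. The same formula gives 1,085.4 per arm; divided by 0.95 this is 1,142.5, or about 2,285 in total, some 200 above 2,082.

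**3. Power of 2,082 on that basis.** Evaluable per arm: 1,041 × 0.95 = 989.

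- Two proportions: Φ[(0.04269 × √989 − 1.960 × 0.50227) / 0.50136] = Φ(0.714) = 76.2%.
- Schoenfeld: HR = ln(1 − 0.12671)/ln(1 − 0.1694) = 0.730; events = 989 × (0.1694 + 0.1267) = 293; power = Φ(√293 × |ln 0.730|/2 − 1.960) = 76.8%.
- Events for 80% at HR 0.730: 4 × (1.960 + 0.842)²/(ln 0.730)² = 317.

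**4. The planned Cox analysis.** Control hazard = −ln(1 − 0.1694)/3 = 0.0619 per year. With 3.5-year accrual and full loss of the 5% drop-outs:

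| Reading of 28% and of the dilution | Diluted HR | Events for 80% | 5-year total: events, power | 5.5-year total: events, power |
|---|---|---|---|---|
| Three-year risk ratio 0.748 | 0.730 | 317 | 313, 79.5% | 356, 84.4% |
| HR 0.72, diluted on the log scale (0.72^0.9) | 0.744 | 359 | 315, 74.7% | 359, 80.0% |
| HR reduction diluted to 25.2% | 0.748 | 372 | 316, 73.2% | 360, 78.6% |

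**5. Is the head-count route unique?** No. The middle row at 5.5 years, divided by 0.95, needs 2,082.2 patients in total. HR 0.72 with three-year risks and drop-out only, with no allowance for non-adherence, gives about 2,080.

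**The case against.** A reader might infer from the match at 1,041 that the allowance was certainly a head count and that 80% is a proven arithmetic error. The article does not support that. It says only that the two allowances were considered. The 20% route counts the 5% drop-out twice and spreads an intervention-arm allowance over both arms, and it was found by trying several inflations. A calculation that does dilute the effect, on the log-hazard scale with a 5.5-year close, reaches 2,082 just as closely.

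Nor is 76–77% the single power of the trial. Alpha is not stated; at one-sided 5%, the diluted three-year calculation gives 80.3–85.3%. Mean follow-up is about 3.25 years (5-year total) or 3.75 years (5.5-year total), so more events accrue than three-year risks imply. On the risk-ratio reading the Cox analysis is within a point of 80% at 5 years, and it reaches 80.3% if drop-outs count until they are lost. The 200-patient gap exists only under the three-year proportions test, which is not the planned analysis. A condensed article may also leave the formula to the full protocol.

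These points remove the claim about the cause and the flat claim of a shortfall. They leave the main point standing: at two-sided 5% with dilution and full loss of drop-outs, neither the three-year basis nor the stated 5-year total reached 80% on any effect reading tried. The planned revisions do not settle this by themselves. The blinded interim analysis looks at the overall event rate and drop-out and does not mention non-adherence. The re-adjustment after 500 patients' blood pressure data will reuse this calculation.

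**Conclusion.** The point holds in conditional form. On the article's three-year basis, reading 28% as a risk ratio, 2,082 patients give about 76–77% power once the 10% non-adherence dilutes the effect, which is 3 to 4 points below the stated 80%. For the planned Cox analysis the figure is about 73–79.5% at the stated 5-year total and about 79–84% at 5.5 years. The spread comes from whether 28% is a risk ratio or a hazard ratio and from the scale of dilution.

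All of this assumes two-sided 5%, no benefit in non-adherers, total loss of drop-outs and, for the Cox figures, a constant hazard. If events concentrate early, the risk-ratio reading yields about 300 events at 5 years and 78% power. Confidence is high in the three-year arithmetic. That a head-count allowance explains the 1,041 remains an inference.

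**What to change.** Restate the power for the planned Cox analysis in one paragraph that gives:

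- the two-sided alpha;
- whether 28% is a three-year risk ratio or a hazard ratio, and how the 10% non-adherence enters;
- the diluted hazard ratio (0.73 if 28% is a three-year risk ratio) and the events needed for 80% (about 317 at that ratio);
- the events expected at the close-out date, after reconciling the 5-year total with 3.5 years of recruitment plus 2 years of minimum follow-up.

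If the three-year basis is kept, report about 77% power. When the effect size is re-adjusted after the first 500 patients, say whether the 10% is applied again: if the blood pressure difference is taken over all randomised patients, it already contains the dilution.

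The cost is one paragraph of wording and a slightly less favourable stated power. No extra patients are required.

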### Statistical analysis

The primary analysis is a time to event analysis using Cox-regression-models. An interim analysis after 160 observed events will be done by a statistician blinded to the study arm. The interim analysis will indicate whether the sample size and study duration has to be modified according to the overall observed event rate. The sample size needs not to be adjusted for this blinded interim analysis as only the overall event rate will be considered. The assessment of the true drop out rate will be part of the (blinded) interim analysis. The dichotomized secondary endpoints will be evaluated according to the primary outcome measure. Continuous variables will be analyzed with the appropriate tests. The clustering of the data by the different centres will be accounted for by using frailty models [20].

### Methods against BIAS

Follow-up assessment are planned to be done by study nurses not involved in providing the individual support program for the patient aiming to keep them blinded to the study allocation. Endpoints will be assessed in a written questionnaire that will be handed out to the patients prior to further follow-up assessments.

The primary endpoints and serious adverse events will be verified and adjudicated by the Endpoint and SAE Adjudication Committee that is blinded to the trial allocation of the individual patients.

### Ethical considerations

The trial does not include any experimental treatments but compares usual care with more intensive care based on national and international guidelines aiming at an improved adherence to evidence based recommendations. The study has been approved by the Ethics Committee of the Charité (EA2/084/11). Patients are insured against travel accidents.

## Discussion

Depending on aetiology, the natural risk for stroke recurrence during the first year after event has been described between 5% [2] (stroke patients without high risk factors) and 20% [15,21-24]. A secondary ischemic event has considerably more serious consequences leading to physical disability in more than 60% and death in more than 20% [25]. In addition to the medical and personal impact of the recurrent stroke, the costs of recurrent events and rehospitalisation are enormous. Lifetime costs per first ever stroke case are more than 40.000 Euro in Germany [26].

Growing evidence suggests that early diagnostic work-up with consequent initiation of multimodal preventive measures results in a major reduction of re-events. In patients with TIA, the “effect of urgent treatment of transient ischemic attack and minor stroke on early recurrent stroke” (EXPRESS) study was conducted as a population based sequential comparison [27]. It demonstrated that urgent assessment of stroke aetiology and early start of secondary prevention was associated with reduced risk for recurrent stroke. The interventions comprised immediate start of poly-pharmaceutical risk factor control, antithrombotic therapy and interventional treatment for symptomatic carotid stenosis. However, patients were followed-up for only three months. Very similar effects were found in the SOS-TIA study with much lower recurrence rates as expected according to the ABCD [2] score [17].

Hence, it seems of crucial importance to start a secondary prevention program at an early stage after the cerebrovascular event. This is particularly important because shortly after the index event, patients are generally very motivated for participation in a structured support program.

In contrast to other diseases such as diabetes mellitus, coronary heart disease and COPD, stroke has not been selected for chronic disease management programs in Germany. Therefore, neither hospitals nor primary care physicians are able to offer intensive monitoring of cardiovascular risk factors to patients after stroke or TIA. Recommendations given in discharge letters frequently focus on medical treatments but not on recommendations regarding non-pharmacological treatments such as life style modifications including physical activities and dietary aspects. Family members are usually not involved in the treatment concepts. Since lifestyle is strongly influenced by the social network, patients frequently continue the unhealthy lifestyle. Smoking, poor diet coupled with physical inactivity and alcohol consumption are still leading causes of mortality [28].

While the primary objective of INSPiRE-TMS is to investigate the effects of a structured multifactorial support program on the vascular re-event-free survival time, a number of completed or ongoing randomized studies examine effects of supported secondary prevention on differences in risk factor control, medication adherence or surrogate parameters. To our knowledge, none of them has been adequately powered to detect a difference in vascular recurrence free survival time [29-38].

Some limitations of the study will need to be considered: First, there is a potential contamination effect in patients who are randomized to the control group. With the information given before randomization and during follow-up visits, these patients may be better informed about effective vascular prevention compared to the normal post-stroke population. This effect is frequently seen in prospective controlled trials. However, it seems unlikely that this contamination will lead to the same effect as the structured intervention program. Second, the information about life style parameters, adverse events and endpoint events will be self-reported. Thus, self-reported errors are to be expected in both groups and expectation bias by study personnel may occur in follow-up documentation. In order to control for these biases, follow-up assessment is planned to be done by study nurses blinded to the trial arm and not involved in the individual support program. The primary endpoints and serious adverse events will be documented in a written form by the patient prior to the follow-up-interview and will be adjudicated by a blinded Endpoint Committee. Third, the study is conducted in two European health systems and generalizability of the study results may therefore be questioned. However, the methods of intervention are standardized as far as possible in individual counseling and both the quality of risk factor control and rate of recurrent events will be described in detail in the control and intervention arms. This should allow a projection of the study results into other health systems.

In summary, the INSPiRE-TMS trial is designed to answer the question whether a structured support program for secondary prevention after a cerebrovascular event is effective in reducing new major vascular events. The results of the trial are expected for the year 2016.

## Abbreviations

BI: Barthel Index; BP: Blood pressure; BMI: Body Mass Index; CHD: Coronary Heart Disease; COPD: Chronic Obstructive Pulmonary Disease; CRP: (C Reactive protein); DWI: Diffusion-Weighted Imaging; HbA1c: Hemoglobin A 1c; INR: International Normalized Ratio; INSPiRE-TMS: Intensified Secondary Prevention Intending a Reduction of Recurrent Events in TIA and Minor Stroke Patients; KKS: Center for Clinical studies (Zentrum fuer Klinische Studien); LDL: Low density lipoprotein; MRI: Magnetic Resonance Imaging; MOCA: Montreal cognitive assessment; mRS: Modified Rankin scale; NASCET criteria: North American Symptomatic Carotid Endarterectomy Trial criteria; NIHSS: National Institutes of Health Stroke Scale; PCP: Primary care Physician; SAE: Serious adverse event; TIA: Transient ischemic attack; TOAST criteria: Trial of ORG 10172 in Acute Stroke Treatment criteria.

